### Aims and hypothesis

The primary aim of this study is to evaluate the efficacy of COS versus TAU in mothers with mental disorder and their infants in promoting attachment security in the child under standard clinical outpatient conditions. More specifically, the goal of the study is to determine whether COS intervention results in more securely attached infant–mother dyads than the control condition (TAU). The primary hypothesis is that the COS intervention will bring about a higher rate of securely attached children after treatment and at follow-up (when the children are aged 16–18 months) than TAU. Secondary hypotheses being tested by the study are that i) COS intervention will lead to an increase in sensitive behavior in mothers, ii) COS intervention will result in an increase in mothers’ ability to mentalize, and iii) COS intervention will improve mothers’ state of mind with regard to their own attachment, relative to TAU.

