[86]) is a self-report measure consisting of 120 items for parents with children aged from 0–12 years, capturing child-related and parent-related stress domains. A total stress score is derived, indicating the severity of the subjective burden of parenting. A domain of life events allows for the recording of positive and negative life events. The PSI is measured at baseline and follow-up.

**DERS –** The Difficulties in Emotion Regulation Scale
[87] is a 36-item self-report on clinically relevant emotion regulation difficulties, especially with regard to negative emotions. Items are scored on a 5-point Likert scale ranging from 1 (almost never) to 5 (almost always). The authors have confirmed a six-factor structure of emotion regulation, upon which the DERS is based; and adequate internal consistency (Cronbach’s α > .80) of these subscales has been established
[87]. For the purpose of this trial, the DERS was translated into German. First, the scale was translated from English to German independently by two translators who then discussed their translations and combined them to form a draft of the questionnaire used in the present study. This draft was back-translated into English by a professional translator. The back-translated version was found to be consistent with the original DERS version. The DERS is applied at baseline and follow-up.

**CBCL** – The Child Behavior Checklist1½**-**5
[88] (German version) is a questionnaire for parents of children aged 1.5-5 years, which is used to assess child behavioral and emotional problems. The items are related to seven problem scales, loading on externalizing, internalizing, and a total score. In the current trial, the CBCL will be administered at follow-up.

**FBB-E** – Fragebogen zur Beurteilung der Behandlung – Eltern
[89] (“A Questionnaire to Evaluate Treatment Satisfaction – Parent Version”) is a well-known German language questionnaire for evaluation and quality assurance of the therapeutic treatment of children, adolescents and their families. The FBB-E assesses how positively or negatively parents evaluate the course and outcome, as well as their personal satisfaction regarding the psychotherapeutic treatment of their children, independent of treatment modality. The FBB-E will be applied at follow-up.

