### Secondary outcomes

a. To compare differences between COS and TAU on maternal sensitivity (MBQS, DIP) as continuous secondary outcome variables, a 2x2 analysis of covariance (ANCOVA), with repeated measurement (t0-t1) on one first factor, will be used. In these analyses, treatment modality will be treated as the second factor, maternal sensitivity as the dependent variable, and maternal psychopathology (BDI, SCL-90-R) and maternal parenting stress (PSI) as co-variables.

b. To compare differences between COS and TAU on maternal mentalization (RF, PRFQ-1) as continuous secondary outcome variables, a 2×2 analysis of covariance (ANCOVA), with repeated measurement (t0-t1) on one first factor, will be used. In these analyses, treatment modality is to be treated as the second factor, maternal mentalization as dependent variable, and again, maternal psychopathology (BDI, SCL-90-R) and maternal parenting stress (PSI) as co-variables.

c. Furthermore, in a multiple linear regression, the differences in maternal sensitivity and mentalization will be used to predict psychopathology and maternal stress (with treatment modality, differences in psychopathology, and differences in maternal distress as independent variables).

d. Before analyzing the proportions of mothers whose attachment representations change during the treatment and follow-up period in both treatment arms, we will separate those mothers with a positive shift in attachment representations [i.e., insecure (-dismissing, preoccupied, unresolved) to secure) from the mothers without such a shift or with a negative one ((i.e., secure to any of the others)]. For binary responses, a binary logistic regression will be used to compare proportions of mothers whose attachment representations (positive shift vs. no/negative shift) have been altered as a criterion variable, and treatment group (COS vs. TAU), differences of maternal psychopathology (BDI, SCL-90) as well as parenting stress (PSI) prior and after treatment as predictor variables.

e. To examine associations between changes of psychopathology (BDI, SCL-90) and changes in parenting stress (PSI) between pre- and post-assessment, a Pearson correlation analysis with the difference scores will be conducted.

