f. Child behavior and emotional problems (CBCL11/2) at follow-up will be analyzed with respect to mean scores in either arm of the trial, using multiple linear regression analyses. Again, maternal psychopathology (BDI, SCL-90) and maternal parenting stress (PSI) will be treated as predictor variables, in addition to treatment modality.

g. Further multiple regression analyses will be conducted, with mean changes in maternal sensitivity (MBQS, DIP), mentalization (RF, PRFQ-1), and maternal attachment representations (positive shift, no/negative shift) before and after treatment, as predictor variables.

h. Binary logistic regression models will be used to compare proportions of child attachment security (vs. insecurity) at follow-up as criterion variables, using treatment modality, maternal sensitivity, maternal self-reflection (RF), maternal psychopathology (BDI, SCL-90), and maternal parenting stress (PSI) as predictor variables.

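### Item d, the only listed between-arm test of hypothesis iii, adjusts for post-randomisation changes in distress, so its treatment coefficient need not equal the effect of COS

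*Protocol article*

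**What the plan says.** Aims and hypothesis states the third secondary hypothesis as a randomised contrast: "COS intervention will improve mothers’ state of mind with regard to their own attachment, relative to TAU".

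Statistical methods, Secondary outcomes, item d gives its analysis: "a binary logistic regression will be used to compare proportions of mothers whose attachment representations (positive shift vs. no/negative shift) have been altered". The predictors are treatment group together with "differences of maternal psychopathology (BDI, SCL-90) as well as parenting stress (PSI) prior and after treatment as predictor variables".

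The measure descriptions and Table 1 place the BDI, SCL-90-R, PSI and AAI at both baseline and follow-up. Item e then correlates "changes of psychopathology (BDI, SCL-90) and changes in parenting stress (PSI) between pre- and post-assessment" as difference scores, which supports reading item d's covariates as change scores too. The wording could also mean that PSI enters as two separate values. Either way, a value from the follow-up visit is in the model.

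No other listed analysis has maternal attachment representation as its outcome. Item g uses the shift only as a predictor. Item d is not labelled exploratory or mediational.

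**The concern.** Randomisation balances what exists before treatment. Changes in BDI, SCL-90 and PSI arise after allocation and are measured at the same follow-up as the outcome. If COS alters them, conditioning on them does two things.

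- It removes from the treatment coefficient any effect on attachment shift that works through reduced distress.
- It compares mothers with equal distress change, who are no longer comparable between arms if something unmeasured (life events or concurrent medication, for example) drives both distress change and shift.

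The route is not far-fetched on the article's own terms. The Abstract lists maternal psychopathology at baseline and follow-up among possible moderators or mediators, although for child attachment. At stake is the one listed between-arm answer to hypothesis iii.

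**Working it through.** The article gives no figure for item d; its sample-size figure belongs to the primary chi-square test. The check is therefore of the model's structure. From the article come 1:1 allocation, 36 per arm (Limitations), and the predictors in item d. All effect sizes below are assumptions.

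**Step 1: mechanism, one change score, 400,000 simulated mothers.** T is treatment, U an unmeasured shared cause, and M the distress change (negative means improvement):

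M = −a·T − u·U + √(1−u²)·e

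logit P(shift) = −1.2 + δ·T − β·M + γ·U

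| Scenario | δ | a | β | u | γ | P(shift) TAU, COS | OR, T only | OR, T and M |
|---|---|---|---|---|---|---|---|---|
| COS does not move M | 0.5 | 0 | 0.8 | 0 | 0 | 0.257, 0.353 | 1.58 | 1.67 |
| Full mediation | 0 | 0.5 | 0.8 | 0 | 0 | 0.257, 0.329 | 1.42 | 0.99 |
| Partial mediation | 0.5 | 0.5 | 0.8 | 0 | 0 | 0.256, 0.436 | 2.25 | 1.67 |
| No effect on shift, shared cause | 0 | 0.5 | 0 | 0.7 | 1.0 | 0.269, 0.270 | 1.00 | 0.72 |
| Same, sign of shared cause reversed | 0 | 0.5 | 0 | 0.7 | −1.0 | 0.270, 0.269 | 0.99 | 1.37 |

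Two hand checks:

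- Row 2: (0.329/0.671)/(0.257/0.743) = 0.490/0.346 = 1.42.
- Row 4: M has unit variance within arm, so at a given M the mean of U is lower under COS by 0.7 × 0.5 = 0.35. With γ = 1.0 the log odds ratio is about −0.35, and exp(−0.35) = 0.70, close to the simulated 0.72.

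Row 1 shows that when COS leaves distress alone, the only difference is the usual gap between conditional and marginal odds ratios.

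**Step 2: trial-like setting.** 36 per arm, three change scores correlated 0.6 within arm, model with treatment plus all three; odds ratios are large-sample limits. Ranges cover repeated simulations.

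No COS effect on shift (true OR 1.0; the treatment-only test rejects in about 4–6%):

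| Shared cause | Fall in distress under COS | Adjusted OR | False rejection |
|---|---|---|---|
| Moderate (correlation 0.3, log-OR 0.5 per SD) | 0.2 / 0.3 / 0.5 / 0.8 SD | 0.96 / 0.95 / 0.91 / 0.86 | 4–7% |
| Strong (correlation 0.6, log-OR 1.2 per SD) | 0.2 SD | 0.86 | 6% |
| Strong | 0.5 SD | 0.63–0.65 | 9–12% |
| Strong | 0.8 SD | 0.50–0.51 | 16–21% |

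True COS effect on shift:

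- Full mediation: OR 1.53–1.54 becomes 1.00–1.02 (0.5 SD fall); OR 1.88–2.01 becomes 0.99–1.01 (0.8 SD fall).
- Real effect with the strong shared cause and a 0.5 SD fall: OR 2.37 becomes 1.70, and power drops from 39–43% to 15–17%.

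**Step 3: events available.** If 28–38% of 72 mothers shift (an assumption), 0.28 × 72 = 20 to 0.38 × 72 = 27 events are expected. Treatment plus three covariates leaves 20/4 = 5 to 27/4 ≈ 7 events per predictor.

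**The case against.** The strongest reply is that the bias may be small. None of the three secondary hypotheses says that COS lowers BDI, SCL-90 or PSI relative to TAU. TAU is active treatment by trained clinicians, and both arms may receive medication and individual psychotherapy, so the between-arm difference in distress could be slight. The large distortions need both a substantial fall in distress and a strong shared cause. This stands, and it limits the size of the point. It does not remove it: the plan cannot know in advance that COS leaves distress unchanged.

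A second reply is that item d may be meant as an explanatory model. Then hypothesis iii has no listed test, and a wording change is still needed. A third is that covariate detail belongs in a fuller plan. That does not cover item d, which names its predictors and their timing.

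Power is also low whichever covariates are used. At an odds ratio of about 2.4 the treatment-only test has roughly 40% power, so a non-significant result would often occur anyway.

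A reader might extend the criticism to items a, b, f and h, which use the same instruments. The text does not support that:

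- Items a, b and f do not state a time point, and a condensed article may leave that to the full plan.
- Item f says only that "maternal psychopathology (BDI, SCL-90) and maternal parenting stress (PSI) will be treated as predictor variables, in addition to treatment modality". The PSI is described as "capturing child-related and parent-related stress domains", but a child-behaviour outcome would be adjusted partly for itself only if a follow-up or change PSI were used, which is not stated.
- Item h models child attachment "using treatment modality, maternal sensitivity, maternal self-reflection (RF), maternal psychopathology (BDI, SCL-90), and maternal parenting stress (PSI) as predictor variables", but the randomised comparison for that outcome is already the unadjusted chi-square test.

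**Conclusion.** The point holds for item d. Its treatment coefficient need not equal the effect of COS, because it conditions on variables measured after randomisation that COS may alter. It drops any effect that runs through distress, and a shared cause can bias it in either direction.

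A reader might infer that the coefficient is certainly not the COS effect, or that a null effect would generally look like harm. Neither follows. The distortion is near zero if COS does not move distress. It is modest with a moderate shared cause, where false rejection stays close to nominal, and large only under strong assumptions that the article neither states nor excludes. Complete loss of a real benefit likewise requires full mediation through distress.

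The consequence is confined to one secondary hypothesis; the primary test is unaffected. The change should be made because the risk is avoidable at almost no cost.

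**What to change.** Change item d only. Test hypothesis iii by comparing the proportion with a positive shift between arms, either unadjusted or adjusted only for baseline (t0) BDI, SCL-90-R and PSI. State in advance which of the two is the main result, since marginal and conditional odds ratios differ slightly. Keep covariates few: with some 20–27 events, the unadjusted comparison or a subset of the baseline measures is easier to support than all three correlated scales.

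Keep the change-score model as a separate exploratory analysis, and state that its treatment coefficient is not reported as the effect of COS.

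The cost is a wording change. Baseline values are already collected in both arms, and the association between distress change and attachment shift can still be shown in the exploratory model.

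### Item e correlates symptom change with parenting-stress change with no term for treatment arm, so any COS effect on both would be mixed into the coefficient (minor)

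*Protocol article*

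**What the plan says.** Item e of the Secondary outcomes section states its purpose as "To examine associations between changes of psychopathology (BDI, SCL-90) and changes in parenting stress (PSI) between pre- and post-assessment". Its method is that "a Pearson correlation analysis with the difference scores will be conducted". It mentions no adjustment for arm, no stratification and no partial correlation. It does not say outright that the arms are pooled, but that is the natural reading.

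The neighbouring items handle treatment explicitly:

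- Items a and b make treatment modality a factor in the repeated-measures ANCOVA.
- Item c is a regression "with treatment modality, differences in psychopathology, and differences in maternal distress as independent variables".
- Item d lists "treatment group (COS vs. TAU), differences of maternal psychopathology (BDI, SCL-90) as well as parenting stress (PSI) prior and after treatment as predictor variables".
- Item f says that the maternal measures "will be treated as predictor variables, in addition to treatment modality".
- Item h models child attachment security "using treatment modality, maternal sensitivity, maternal self-reflection (RF), maternal psychopathology (BDI, SCL-90), and maternal parenting stress (PSI) as predictor variables".

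Item g is the only other item that does not name treatment. It reads: "Further multiple regression analyses will be conducted, with mean changes in maternal sensitivity (MBQS, DIP), mentalization (RF, PRFQ-1), and maternal attachment representations", followed by the coding of the attachment shift. It names no dependent variable.

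**The concern.** In a two-arm trial, a correlation taken over everyone has two sources: the association between the variables among mothers in the same arm, and the difference between arms in both means. If COS moves symptoms and parenting stress relative to TAU, the second source contributes even when the two changes are unrelated within each arm. The coefficient then partly restates two treatment effects.

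Item e is meant to show which changes go together. The abstract names psychopathology among the candidate moderators and mediators of attachment security, so a COS effect on symptoms is at least contemplated. A pooled change-change correlation could be taken as evidence of a link within mothers when part of it is the arm contrast.

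**Working it through.** **Plan's own figure.** The article attaches no number to item e, so there is none to reproduce. The only power calculation is for the primary chi-square test.

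**Inputs from the article.** Allocation is 1:1 (Randomization procedures). The adopted sample is N = 72, 36 per arm (Limitations), and the calculated sample is N = 80 (Sample size and power).

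**Assumptions, not in the article.** d1 and d2 are the standardised COS-minus-TAU differences in the two change scores. Change scores are normal with equal within-arm variance in both arms, there is no drop-out, and tests are two-sided at 5%.

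**Formula.** With half the sample in each arm and within-arm SD 1, the arm difference adds d²/4 to each variance and d1·d2/4 to the covariance. With within-arm correlation ρ:

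pooled r = (ρ + d1·d2/4) / √[(1 + d1²/4)(1 + d2²/4)]

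**Zero within-arm correlation (ρ = 0):**

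- d1 = d2 = 0.3: 0.0225 / 1.0225 = 0.022
- d1 = d2 = 0.5: 0.0625 / 1.0625 = 0.059
- d1 = 0.5, d2 = 0.8: 0.10 / √(1.0625 × 1.16) = 0.090
- d1 = d2 = 0.8: 0.16 / 1.16 = 0.138
- d1 = 0.5, d2 = 0: 0

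**Rejection rates by simulation** (40,000 replicates per scenario):

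| d1, d2 | Pooled r | Pooled test, N = 72 | Pooled test, N = 80 | Adjusted for arm |
|---|---|---|---|---|
| 0.3, 0.3 | 0.02 | 5.5% | 5.3% | about 5% |
| 0.5, 0 | 0.00 | 5.0% | 4.9% | about 5% |
| 0.5, 0.5 | 0.06 | 7.8% | 8.2% | about 5% |
| 0.5, 0.8 | 0.09 | 11.9% | 12.4% | about 5% |
| 0.8, 0.8 | 0.14 | 21.3% | 23.4% | about 5% |

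The simulated mean correlations agree with the formula. The partial correlation given arm averages zero throughout, with rejection rates of 4.9% to 5.1%.

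**Non-zero within-arm correlation.** If ρ = 0.5 and d1 = d2 = 0.5, pooled r = (0.5 + 0.0625) / 1.0625 = 0.53, a shift of 0.03. If the effects had opposite signs (+0.5 and -0.5) and ρ = 0.4, pooled r = (0.4 - 0.0625) / 1.0625 = 0.32, so a real association would be understated.

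**The case against.** The best defence is that item e is descriptive. It sets out to examine associations, and a pooled Pearson coefficient is a valid estimate of the overall association in the sample. Preferring the within-arm association is a choice of target. The item claims no mechanism, the mediation aim in the abstract concerns attachment security and does not list parenting stress, and item h, which models attachment security, includes treatment. All of this stands, and it limits the weight of the point. It does not remove it, because the pooled figure cannot tell the reader how much of it is the arm difference, and separating the two costs almost nothing.

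The second defence is that the bias needs COS effects on both variables. The secondary hypotheses cover sensitivity, mentalizing and state of mind with regard to attachment. They do not cover BDI, SCL-90 or PSI. TAU is active treatment, and both arms may receive medication and individual psychotherapy. This also stands.

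The third is that zero within-arm correlation is unlikely for self-reports from the same mother at the same visits. With a moderate positive correlation the distortion is small, as the 0.50 to 0.53 example shows. The masking case needs COS to move symptoms and parenting stress in opposite directions, which nothing in the article suggests.

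A reader might also infer that item g omits treatment, and that the problem is sharper there because its predictors are what COS is hypothesised to change. The text does not establish this. The sentence names no outcome, so its predictor list cannot be taken as complete. It also opens as a continuation of item f, whose models contain treatment modality.

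**Conclusion.** The point holds for item e and is minor. The stated method has no term for arm, unlike six of the eight items, and a COS effect on both change scores would enter the coefficient. Under zero within-arm correlation the induced r is about 0.02 to 0.06 for effects of 0.3 to 0.5 SD on both variables, with rejection in about 5.5% to 8% of trials at N = 72. It reaches 0.14 and about 21% only at 0.8 SD on both. It is nil if COS affects only one of them.

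Two stronger readings of the size are not supported. One might take the medium effect of w = 0.3 in Sample size and power as the plan's own assumption for these scores, but it belongs to the primary chi-square test on child attachment. One might also quote still larger shifts, such as 1.0 SD on both (r = 0.20, about 40% rejection at N = 72), but the article gives no basis for effects of that size on self-reported symptoms and stress against active TAU.

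For item g the most that can be said is that the article does not show whether treatment is in the model. Neither the primary comparison nor the tests of the three secondary hypotheses depend on item e.

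**What to change.** In item e, report the partial correlation of the difference scores adjusted for treatment arm, for BDI with PSI and for SCL-90 with PSI. Give the two within-arm correlations alongside, so that the reader can see whether the association is similar under COS and TAU. For item g, confirm that treatment modality is among the predictors, as in item f.

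This is a change of wording in the analysis section and needs no new data. It costs one degree of freedom per correlation: at N = 72, from 70 to 69.

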#### Randomization procedures and methods to minimize bias

Eligible patients were randomly assigned to the COS intervention or TAU in a ratio of 1:1. An electronic randomization list was generated using Randlist 1.2 as a random generator. Unique randomization numbers were generated to ensure that the study arm assignment was unbiased. Randomization was stratified for two infant age groups (4–6 months vs. 7–9 months) and separate random lists were created for each age group. Block sizes of six to eight were used for the randomization of the treatment arms. The randomization list was generated by the randomization representative and was stored in a password-protected electronic document accessible only by the randomization representative. Each random number was stored in a concealed randomization envelope. After a patient’s eligibility for the study was determined, the next available randomization number was assigned to the patient, in ascending order. To minimize bias that could have arisen from knowledge of treatment allocation, all outcome assessors were blind to treatment allocation and a random sample of outcome measures was re-rated by independent assessors.

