### Statistical methods

#### Sample size and power

The primary outcome for treatment efficacy is the rating of quality of child attachment at follow-up at children’s age 16–18 months (COS vs. TAU) by an objective rater blind to treatment allocation. Differences in distributions of the quality of child attachment (secure vs. insecure-avoidant, -resistant, -disorganized) between both treatment modalities are calculated by a chi-square test of significant statistical independence. A power analysis for comparing COS and TAU with a power of 80% and the probability of making a Type I (α) error of 5%, with a medium effect (*W* = 0.3) suggested a recruited sample size of N = 80.

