### Limitations

The circumstances of this clinical trial necessitated some scientific compromises. One limitation of this trial is that the person who oversaw the implementation of the COS intervention is also the principle investigator. Thus, personal factors (allegiance effects) may limit the generalizability of our findings. In view of the fact that the study sample comprises clinically referred mothers with mental disorders and their infants, it is ethically unacceptable to use a no-treatment control group. Therefore, in the best interest of our patients we have used TAU as the control intervention to which patients are randomized. According to the natural flow of patients attending the outpatient unit, eligible women with infants participated voluntarily, and, having given their informed consent, were randomly assigned to COS or TAU. Thus, our clinical sample varied in terms of psychopathology. There may be a sampling bias, insofar as the mothers with infants attending the outpatient unit might represent a more severely mentally disordered sample choosing to participate in this trial. This may limit the generalizability of the findings, due to sampling bias and a lack of true representativeness. Hence, replication studies or a multi-site trial are necessary. A sample size of N = 80 was determined before any data were collected, based on the assumption of medium effect size and power. For practical reasons, we defined a sample size of N = 72, such that 36 mother-infant dyads were randomly assigned to COS (six COS therapeutic groups) and 36 mother-infant dyads to TAU. Further long-term follow-up measures might be useful to capture positive changes of the intervention that may be attributable to a sleeper-effect
[66] and apparent only at later follow-up stages.

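### If items d and h are fitted by standard maximum likelihood, 3 to 6 events per slope would overstate non-null conditional log odds ratios by roughly 10–30% on average

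*Protocol article*

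**What the plan says.** Two of the models listed in the Protocol article under Secondary outcomes have a binary response.

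- **Item h (child attachment):** "Binary logistic regression models will be used to compare proportions of child attachment security (vs. insecurity) at follow-up as criterion variables". The predictors are treatment arm, maternal sensitivity, reflective functioning, BDI, SCL-90 and PSI. Item a of the same list defines sensitivity by two measures, MBQS and DIP.
- **Item d (maternal representations):** "a binary logistic regression will be used to compare proportions of mothers whose attachment representations (positive shift vs. no/negative shift) have been altered". The predictors are treatment arm and the pre-to-post differences in BDI, SCL-90 and PSI.

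On size, the section Sample size and power says the calculation "suggested a recruited sample size of N = 80". Limitations then says: "For practical reasons, we defined a sample size of N = 72", that is, 36 dyads per arm.

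The article gives no expected rate of secure attachment, no rate of positive shift and no drop-out rate. It does not name an estimator beyond binary logistic regression.

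**The concern.** Maximum-likelihood logistic regression has a known small-sample bias. When events per slope are few, log odds ratios that are not zero are on average estimated too far from zero. With few events in one arm there may also be no finite estimate. Both models carry many slopes for 72 dyads, and BDI and SCL-90 overlap in content, which adds imprecision.

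Item d is the only listed between-arm analysis for secondary hypothesis iii (mothers' state of mind regarding attachment). Item h is the only listed model that names child security as the outcome and has maternal predictors; item g names no outcome. The Abstract says these data are meant to give preliminary indications about moderators and to inform hypotheses about which intervention suits this setting. The odds ratios are therefore likely to be read as effect sizes.

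**Working it through.** **1. The plan's own figure.** The only stated size calculation is for the primary chi-square test (w = 0.3, 5% error, 80% power). With one degree of freedom and a two-sided test, N = (1.960 + 0.842)² / 0.3² = 7.85 / 0.09 = 87.2, so 88 rather than 80. Power is 76.5% at N = 80 and 72.1% at N = 72. That is a separate matter. The plan states no event count or odds ratio for items d and h that could be reproduced.

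**2. Events per slope in item h.** The smaller of two outcome classes among 72 children is at most 72 / 2 = 36.
- Six slopes: 36 / 6 = 6.0. Seven slopes: 36 / 7 = 5.1.
- At N = 80 the ceilings would be 40 / 6 = 6.7 and 40 / 7 = 5.7.
- If the smaller class is an assumed 29–46% of 72 (21 to 33 children), the range is 21 / 7 = 3.0 to 33 / 6 = 5.5.

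The ceiling needs no assumed rate. The lower range does.

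**3. Events per slope in item d.** Assuming 15–26% of 72 mothers shift positively (11 to 19), the range is 11 / 4 = 2.8 to 19 / 4 = 4.8. Only mothers who are insecure at baseline can shift positively.

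**4. Size of the bias.** Monte Carlo, 2,000 runs per scenario, maximum likelihood against Firth. All of the following are assumptions: N = 72, or 60 after a loss of 12 / 72 = 17%; treatment odds ratio 1, 2 or 3.5; covariate odds ratio 1.5 per SD; some covariates correlated at 0.6. Averages leave out data sets without a finite estimate.

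| Item | N | Events | Slopes | True OR | Exp. of mean ML log OR | ML bias in log OR | Bias / SE | Firth bias |
|---|---|---|---|---|---|---|---|---|
| h | 72 | 33 | 6 | 2 | 2.22 | +15.0% | 0.15 | +0.6% |
| h | 72 | 33 | 6 | 3.5 | 4.19 | +14.4% | 0.25 | −0.2% |
| h | 60 | 21 | 7 | 2 | 2.40 | +26.0% | 0.20 | +1.3% |
| h | 60 | 21 | 7 | 3.5 | 4.95 | +27.7% | 0.35 | +2.1% |
| d | 72 | 19 | 4 | 2 | 2.12 | +8.7% | 0.09 | −2.5% |
| d | 72 | 11 | 4 | 2 | 2.20 | +14.0% | 0.11 | 0.0% |
| d | 60 | 11 | 4 | 3.5 | 4.23 | +15.1% | 0.21 | +3.3% |

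Bias is (mean estimate − truth) / truth on the log scale; in the first row, 0.797 / 0.693 − 1 = 15.0%. Across all non-null scenarios the treatment bias was +14% to +28% for item h and +9% to +15% for item d. In the tabulated size settings, the covariate coefficients were overstated by about 12–31%.

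**5. The most favourable case.** With exactly half the children secure and no drop-out (3,000 runs; true treatment odds ratio 2 or 3; weaker effects for BDI, SCL-90 and PSI), the item h bias at N = 72 was 11–14% with six slopes and 15–16% with seven. Firth was within about 1%.

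**6. What does not go wrong.** At a true odds ratio of 1, the mean treatment log odds ratio was −0.02 to +0.03. Coverage of 95% Wald intervals was 93–98%. The treatment estimate lay further from 1 than the truth in 54–62% of simulated trials, so in about 40% or more it did not.

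**7. Imprecision.** At N = 72 with 33 events, six slopes and a true odds ratio of 3.5, the standard error is 0.72. A 95% interval then spans a factor of exp(1.96 × 0.72) = exp(1.41) = 4.1 either side of the estimate.

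**8. No finite estimate.** This occurred in about 0–0.15% of item h data sets. In item d with 11 events and N = 72 it occurred in 1.35% at an odds ratio of 2 and 5.25% at 3.5; with 19 events and an odds ratio of 3.5, in 0.35%.

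**The case against.** **The estimator is not named, and an analysis plan not shown may name it.** This is true, and it is why the point is conditional. It does not remove it: the article sets out its analysis under a Statistical analysis plan heading and fixes both the model type and the predictor lists. Unqualified logistic regression ordinarily means maximum likelihood. Item h also speaks of models in the plural, so a single simultaneous fit is not certain, and the seventh slope rests on carrying over item a's two measures.

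**The bias is small beside the sampling error.** This stands. Mean bias is 0.09–0.35 of a standard error and interval coverage is adequate. A reader might infer that the odds ratios this trial reports will be inflated. The documents do not support that: the bias is an average over hypothetical trials, it is absent for null effects, and a single estimate may fall on either side.

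**The COS effect may not be overstated at all.** This also stands. A reader might infer that these models exaggerate the benefit of COS. But item d adjusts for changes measured after randomisation, and item h does not say whether its maternal scores are baseline or follow-up values. If follow-up sensitivity and reflective functioning enter, the coefficient excludes the pathways through which COS is meant to act. In simulations of that case (N = 72; assumed COS shift of 0.3–0.8 SD in each mediator; log odds ratio 0.6 per SD; 30% of controls secure), the mean maximum-likelihood treatment odds ratio was below the total effect in 11 of 12 scenarios, for example 2.2 against 3.0. Firth does not correct that and lowers the estimate a little further.

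**The efficacy claim rests elsewhere.** The primary analysis is an unadjusted chi-square test, which is untouched.

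**Conclusion.** The point holds in a conditional and limited form. That item h has at most 5 to 6 events per slope follows from N = 72 and the predictor list alone. The figure of about 3 to 5 for item d, and anything below the ceiling for item h, rests on assumed outcome rates; the article states none, and the counts of 21–33 and 11–19 should not be read as the plan's own.

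Under maximum likelihood, non-null conditional log odds ratios for treatment and maternal predictors would be overstated by roughly 10–30% on average. For treatment, a true odds ratio of 2 would be reported as about 2.1–2.4. At low assumed shift rates, up to about 5% of item d data sets would have no finite estimate. Wide intervals remain the larger limitation of both models. Nothing here bears on the primary test or shows that the total COS effect will be exaggerated. This is a cheap improvement to secondary analyses, not a threat to the trial's main conclusion.

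**What to change.** State that the logistic regressions in items d and h are fitted by Firth's penalised likelihood, with profile penalised-likelihood confidence intervals. In the simulations this brought the treatment log odds ratio to within about 4% of the truth, gave a finite estimate in every data set, and lowered root-mean-square error by about 4–25%.

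Entering only one of BDI or SCL-90-R, chosen before the data are analysed, is optional: Firth alone deals with the treatment bias.

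The cost is one sentence in the analysis plan and standard software, with no new data. The article describes follow-up as still under way, so the choice could be fixed before analysis. The small downside is that reported effects become slightly less favourable.
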